### Patient-administered stimulation

At the first visit subjects are measured up for individually fitted headband locators for electrode placement. Headbands are measured and marked relative to ear tragi, the nose and midline of scalp. A separate occipital band ensures the locator headband cannot slip from its position. Anodal and cathodal electrodes are differently coloured (red and black) and the patient is shown which way around they should be placed. Once fitted, subjects are shown how to position the headbands reproducibly and instructed on how to position the band markers relative to the anatomical landmarks described. Patients are then asked to demonstrate this to the investigator and feedback given until electrodes are correctly and reproducibly positioned. Photographs and measurements are taken in case of the need for reference at home and all instructions are given to the patient in writing also. In this patient information leaflet subjects are informed of potential side effects such as tingling, burning sensation, dizziness, headache, nausea and phosphenes while switching the device on or off abruptly. Electrode placement is re-checked at the beginning of each treatment block.

Programming of devices requires a dedicated programmer with security code access. Overriding or manual reprogramming is not available to patients.

### Study flow

The study will have five phases. At baseline (visit 0, one of their rTMS treatment visits), the patient is given a short presentation of how the tDCS device is used with one of the investigators being the substitute patient. The patient will then receive the Patient Information Sheet and Pain diary. If they wish to join the study they will contact the Research Clerk after having read the information after a minimum of 24 h. The Research Clerk will provide the appointment for visit 1, advising the patient to fill in the pain diary over a minimum of 7 days. At visit 1, eligibility will be determined (as per inclusion and exclusion criteria). Provided they are eligible patients will be recruited and consented. The patient and carer/partner will then be shown how to apply the tDCS device, and the patient will then try it on themselves, with the help of the carer/partner if necessary. The first trial stimulation will be carried out according to the randomisation order by the research assistant. The investigators will then confirm that the patient and carer/partner have understood all details of the stimulation. Following instructions regarding the daily use of the device, a further pain diary is supplied and a subsequent visit agreed in 2 weeks’ time. At this visit (visit 2), the patient will return the pain diary and will surrender the tDCS device. The third visit (3) will be arranged for a further 4 weeks’ time (wash-out period); during the interim a daily pain diary will be kept. At visit 3, the tDCS device will be returned to the patient, and a new stimulation mode will be selected by the research assistant as per the randomisation order. After 2 weeks (visit 4), the tDCS device will again be surrendered to the investigators and the second wash-out period of 4 weeks with diary keeping started. At visits 5 and 6, tDCS device will be received and later surrendered by the patient as during previous treatment arms. The final visit (7) will happen in a further 2 week’s time.

In the case of patients who wish to continue, the tDCS device will be given him/her for regular daily use and visits agreed at 1 month, 3 months, 6 months and 12 months. Before each visit, they are asked to keep a 1-week pain diary to assess their mean pain level.

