**Methods/design:**

This article reports the protocol for a randomised, sham-controlled, double-blinded crossover study in which patients with chronic neuropathic pain (*n* = 24) will receive anodal, cathodal and sham tDCS over M1. All patients will have previously completed a study of rTMS of the motor cortex and have been designated as responders or non-responders to this modality.

Patients receive all three tDCS stimulation types by self-administration. We assess the effect on pain scores [numerical rating scale (NRS)], self reported health status (Short Form-36 Health Survey) and anxiety/depression (Hospital Anxiety and Depression Scale). A linear mixed model with fixed effects will analyse changes in pain scores from pre- to post- interventions. Analysis will be carried out on an intention-to-treat basis. A proportion analysis will also be carried out with patients separated into either responders or non-responders to previous TMS.

Safety will be assessed throughout the study by monitoring of adverse events.

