## Background

Stimulation of the primary motor cortex (M1) of the brain was first shown to reduce central pain in patients by Tsubokawa et al. [1] using implanted electrodes in the epidural space around the brain. More recently, non-invasive methods of cortical stimulation have been tested such as repetitive transcranial magnetic stimulation (rTMS) and transcranial direct current stimulation (tDCS) [2].

Previous research in our laboratory has shown that approximately 40% of chronic pain patients obtained at least 20% improvement in pain scores following high-frequency rTMS of the M1 motor cortex [3] lasting for approximately 2 weeks consistent with other rTMS studies [4,5]. The effect seems to be maintained as long as rTMS sessions continue, but this requires frequent attendances by patients. The proposed study is based on the hope that tDCS could offer an alternative method for cortical stimulation in this group of patients. As portable tDCS devices have become available, patients/carers can be trained in its application and patients may use these at home without the need for regular visits to our laboratory. If proven sufficiently effective, tDCS could offer an economical and convenient way of delivering cortical stimulation for pain relief.

tDCS involves the application of a low-amplitude constant electric current to the scalp, a proportion of which enters the skull to affect cortical activity in the brain. It does not directly induce action potentials in neurons but rather alters the membrane potential and thus influences the excitability of these cells [6,7]. Typically it is applied via two electrodes, an anode and a cathode, with the current travelling from anode to cathode. The polarity however can be changed by reversing the electrode position. Anodal stimulation of the scalp overlying the cortex results in increased excitability of this cortical area whilst cathodal stimulation has the opposite effect [8].

It has been shown to be effective in the treatment of various conditions including motor function recovery following stroke, reduced epileptiform discharges in epilepsy, mood elevation in depression and improvement of motor function in Parkinson’s disease [9-12].

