#### Inclusion criteria

Inclusion criteria include (1) age between 18–85 years; (2) stable analgesic medication for the prior month; (3) mean pain levels ≥4 out 10 on VAS for pain during the 1-week run-in phase, based on patient diary; (4) willingness to take part; (5) ability to consent; (6) previously had a minimum of five sessions of TMS for pain, and can be named as a “responder” or “non-responder” where the responder reports a weekly average pain reduction of 20% on an NRS of 0–10, following five rTMS sessions.

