#### Initial and follow-up assessments

The initial and follow-up assessments will include a record of (1) handedness (not in follow-up assessments); (2) NRS for pain, including measurements for overall daily pain severity, unpleasantness of pain and severity of paroxysmal pain attacks if present. Pain diaries will be filled out daily for 1 week at baseline and for 14 days beginning at each stimulation period [39]. (3) Health status will be assessed by the Short Form 36 Health Survey (SF-36) [39]. (4) Anxiety and depression will be assessed by the hospital anxiety and depression scale (HADS) [40], as well as (5) the mini-mental state examination [41] and (6) patient experience of equipment use, including convenience and adverse effects [39]. Patients are given contact details of medically qualified personnel to contact in case of serious side effects. These will be reported descriptively.

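### The run-in diary may be kept within the roughly 2-week rTMS effect the protocol itself states, which can lower the baseline, mainly in rTMS responders

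*Protocol article*

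**What the plan says.** All references are to the protocol article.

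- **Timing of the run-in.** Study flow describes the first contact thus: "At baseline (visit 0, one of their rTMS treatment visits". The patient receives the diary at that visit and contacts the research clerk "after having read the information after a minimum of 24 h". The clerk books visit 1, "advising the patient to fill in the pain diary over a minimum of 7 days". The first stimulation is given at visit 1.
- **Duration of the rTMS effect.** Background describes the benefit as "lasting for approximately 2 weeks consistent with other rTMS studies", and adds: "The effect seems to be maintained as long as rTMS sessions continue".
- **Use of the run-in.** Inclusion criteria require mean pain of at least 4 "during the 1-week run-in phase, based on patient diary". Statistical analysis uses the run-in as the reference for change scores and for a positive response (a reduction of at least 2 units or 30%).
- **Diary length.** "Pain diaries will be filled out daily for 1 week at baseline and for 14 days beginning at each stimulation period" (Initial and follow-up assessments).
- **Status of rTMS at entry.** The Abstract states: "All patients will have previously completed a study of rTMS of the motor cortex". Patient selection and Sample size calculations also treat rTMS as past. None of these sections gives the time since the last session.

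**The concern.** The design allows 4 weeks of wash-out between tDCS periods, so it recognises carry-over. It states no separation between rTMS and the run-in. The stability requirement in Inclusion criteria covers analgesic medication only.

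If the run-in is recorded while rTMS is still working, the baseline understates the patient's untreated pain. The understatement depends on how well the patient responded to rTMS, and that is the factor on which the hypothesis in Aims divides the patients. Three things are at stake:

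- Patients with a good rTMS response may miss the pain threshold of 4.
- Change from run-in may look too small in rTMS responders.
- The 30%/2-unit rule may be harder for rTMS responders to meet than for non-responders. This works against the protocol's own hypothesis.

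**Working it through.** **The protocol's own figure.** Sample size calculations give p = 0.036 for 8/12 against 2/12 (two-tailed Fisher's exact test). This is reproduced: p = 0.0361. The illustration is fragile: 7/12 against 2/12 gives p = 0.089, and 6/12 gives p = 0.193. A baseline error that reclassifies one rTMS responder is enough to lose significance.

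**Day count on the earliest permitted schedule.** Take visit 0 as the last rTMS session (day 0) and the effect as 14 days.

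- Run-in diary: days 1–7, after the 24-hour minimum. All 7 of 7 days fall within the window.
- Visit 1: day 8. Period 1 diary: days 8–21. Days 8–14, or 7 of 14, fall within the window.
- Stimulation (5 consecutive days): days 8–12, all within the window.
- Periods 2 and 3 start 2 + 4 = 6 and 12 weeks after visit 1, outside the window unless rTMS continues.

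If rTMS sessions continue after visit 0, the overlap is larger. If visit 1 is booked later and the diary is started later, it is smaller or absent.

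**Entry threshold.** If a fraction r of the rTMS benefit remains, the run-in reads T(1 − r), where T is untreated pain. To show 4.0 a patient needs T = 4/(1 − r). That is 5.0 for r = 0.20 (the responder cut-off in Inclusion criteria) and 5.7 for r = 0.30 (assumed).

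**Response rule.** Let B = T(1 − r). A response needs a fall of at least min(2, 0.3B) from B. If no rTMS benefit remains when response is assessed, the fall needed from untreated pain is 1 − [B − min(2, 0.3B)]/T. With T = 7 (assumed; the document gives no expected pain level):

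| Residual r at run-in | B | Pain needed | Fall from untreated pain |
|---|---|---|---|
| 0 | 7.00 | 5.00 | 28.6% |
| 0.10 | 6.30 | 4.41 | 37.0% |
| 0.15 | 5.95 | 4.165 | 40.5% |
| 0.20 | 5.60 | 3.92 | 44.0% |

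The rows for 0.10 and 0.15 can describe non-responders, who are defined by a reduction below 20% and not by no reduction.

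**Opposite limit.** If the 20% residual were still fully present during the assessment, pain on rTMS alone would be 5.6. tDCS would then need to add 1 − 3.92/5.6 = 30%, close to the 28.6% without any residual. Period 1 lies somewhere between these limits. Periods 2 and 3 lie near the 44% limit for a patient whose run-in carried the full 20%.

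**The case against.** **Overlap is possible, not certain.** A reader might infer that the baseline is contaminated. The document does not support that. Seven days is only a lower limit, the clerk sets the appointment, and several sections describe rTMS as past. A patient approached at the final rTMS visit will have completed rTMS by entry, so the Abstract and Study flow sit uneasily together without flatly contradicting each other. This stands. The number of affected patients cannot be known from the article. Still, none of the sections that call rTMS previous gives an interval, so they do not remove the problem.

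**It is not confined to responders.** A reader might also infer that non-responders are untouched. The inclusion criterion defines them by less than a 20% reduction, so they may carry a partial effect. At 15% residual the gap to a responder at the 20% cut-off is 44.0 − 40.5 = 3.5 percentage points, not 15.4. This stands, and the correct word is mainly.

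**The primary comparison is largely safe.** The primary outcome is mean daily pain under each mode, compared by contrasts within patients. One run-in baseline is common to a patient's three periods and cancels in those contrasts, and randomised order spreads any period 1 carry-over across modes. This stands. What remains is that the listed period term is common to both groups, so it cannot absorb a period 1 trend specific to rTMS responders.

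**The required reductions are illustrative.** They assume a full residual at run-in and none later. This stands as well: the document gives no decay curve and no standard deviation.

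**This is a pilot.** It has an opportune sample and no power calculation. That limits the weight of any p-value, but the responder comparison is the one the protocol itself illustrates.

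**Conclusion.** The concern holds in conditional form. Followed as written, the study flow can place the whole run-in and half of the period 1 diary inside the rTMS effect that the article itself states, with nothing to prevent it. The result can be a lowered run-in mean, mainly in rTMS responders. The exposure is limited to the entry threshold, change from run-in, and the 30%/2-unit comparison of rTMS responders with non-responders.

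The direction is towards missing a tDCS response in rTMS responders. At untreated pain of 7 the hurdle rises from 29% to at most 44% for a 20% residual. The gap is smaller in period 1 and against non-responders with a partial rTMS effect. These sizes rest on the assumed pain level and residual, and on visit 0 being at or near the last rTMS session with a prompt visit 1. The document does not support the stronger reading that the primary comparison of modes is biased.

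**What to change.** - **Timing.** Reconcile the Abstract, Background and Study flow so that the diary days used for eligibility and baseline fall outside the rTMS effect the article states. This concerns when the baseline is measured. No change to rTMS treatment is proposed here.
- **Record.** Enter the date of each patient's last rTMS session, including for patients already enrolled, since it may be harder to recover later.
- **Patients already enrolled with overlap.** Keep the run-in baseline in the main analysis. Add a sensitivity analysis that excludes their period 1 data or includes a period-by-responder-group term, and another that repeats the responder comparison without these patients.
- **Do not substitute a wash-out week as the main baseline.** It would be measured after randomisation and after tDCS, whose effects the Background says can persist for several weeks. No such week exists before period 1. Using it only for patients with overlap would also define baseline differently in a group likely to hold more rTMS responders.

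The cost is a later visit 1 for some patients, one extra recorded date and some extra analysis. Excluding period 1 gives up one of three periods for the affected patients in a trial of 24, which is why it belongs in a sensitivity analysis. The trial is still enrolling, so the timing change can still help.

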### Evaluation of tDCS delivery

#### Primary and secondary outcome measures

The primary outcome measure will be the mean daily pain intensity during each mode of tDCS. Secondary outcome measures will be change in hospital anxiety and depression scale (HADS), mini mental state examination and the general health survey (SF 36). Monitoring of device usage will also be recorded, along with patient experience of using the device. At the end of each treatment the device will be returned and interrogated to record actual date, time, duration and number of stimulations delivered and if stimulations were successful.

### Sample size calculations

As this is a pilot study, it is based on an opportune sample of 24 patients who have previously undergone rTMS and expressed willingness to take part in the study. No formal power calculations have therefore been carried out. If, however, 8/12 responders receiving anodal tDCS report a beneficial effect [weekly mean reduction of 30% or 2 units on NRS (0–10) from tDCS] and just 2/12 of non-responders do the same, this itself would give a statistical significance of *p* = 0.036 (two-tailed Fisher’s exact test). Other results would yield important data for future studies (see below).

### Statistical analysis

A linear mixed model will be formed with fixed effects of mode of tDCS, treatment sequence, responder group and treatment period, and the random effect as patient (nested in sequence); the model will be first fitted with the pain intensity data. All patients will be included and all pairwise comparisons will be made with the estimated contrast from this model. Secondary continuous outcome measures will be analysed in the same way as the primary endpoint. Baseline covariates will be incorporated as standard fixed effects but the sensitivity of the results to other ways of incorporating baseline information will be assessed [43]. This information will be used to inform future studies. Where required, change in pain scores pre-post each treatment period will be calculated as the difference between pain during run-in baseline and pain over 3 consecutive weeks following tDCS treatment. Analysis will be performed using Stata software (StataCorp, *Stata Statistical Software*, College Station, TX: StataCorp LP). A proportion analysis will also be carried out with patients separated into responders and non-responders and their response rated as positive (pain reduction from run-in baseline of at least 2 units on VAS 0–10, or 30%) and negative (pain relief less) and analysis carried out separately for the three different tDCS treatments.

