### Aims

The main aim of this study will be to determine the efficacy of home-based tDCS treatment in two chronic neuropathic pain patient populations: responders and non-responders to rTMS. The hypothesis is that those patients who have previously responded to rTMS will also respond to tDCS while non-responders may not. To test this hypothesis TMS responders will be subjected to three different types of tDCS: anodal, cathodal and sham tDCS. In addition, there remains a possibility that tDCS may show efficacy even in those patients who previously have not responded to rTMS. Therefore, non-responders will be subjected to the same three modes of stimulation as responders.

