### Study design

This study will be a randomised, double-blind, double cross-over, sham-controlled trial. Three stimulation modes will be compared: anodal, cathodal and sham stimulation.

Twelve responders and 12 non-responders to rTMS will be randomly assigned to receive anodal, cathodal or sham stimulation as their first treatment session.

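### The mixed model has no tDCS mode × rTMS-responder interaction, so it estimates a pooled effect but cannot test whether the effect differs between the two groups

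*Protocol article*

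**What the plan says.** Under Aims, the protocol article sets out to "determine the efficacy of home-based tDCS treatment in two chronic neuropathic pain patient populations: responders and non-responders to rTMS". It then states: "The hypothesis is that those patients who have previously responded to rTMS will also respond to tDCS while non-responders may not". The Discussion paragraph of the abstract names two goals: efficacy of self-administered tDCS overall, and insight into a possible differential effect by earlier rTMS response. The Study design section builds the sample on that split: "Twelve responders and 12 non-responders to rTMS will be randomly assigned to receive anodal, cathodal or sham stimulation".

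The outcome is continuous: "The primary outcome measure will be the mean daily pain intensity during each mode of tDCS". The model is listed term by term under Statistical analysis: "A linear mixed model will be formed with fixed effects of mode of tDCS, treatment sequence, responder group and treatment period", with "the random effect as patient (nested in sequence"). The section continues: "All patients will be included and all pairwise comparisons will be made with the estimated contrast from this model". Baseline covariates are added as ordinary fixed effects. No product of mode and responder group is listed.

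The only analysis that separates rTMS responders from non-responders is an additional comparison of proportions. A positive response is a fall of at least 2 units or 30% from run-in, with "analysis carried out separately for the three different tDCS treatments". The Sample size section illustrates it under anodal tDCS alone (8/12 against 2/12, two-tailed Fisher p = 0.036) and says that no formal power calculation was done.

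**The concern.** A hypothesis that one group benefits and the other may not is a statement about a difference in treatment effect, that is, a mode × group interaction. In a main-effects model the anodal-sham, cathodal-sham and anodal-cathodal contrasts are constrained to be equal in the two groups. The responder-group coefficient does not fill the gap, because it measures only the difference in mean pain averaged over the three modes.

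The analysis of the continuous primary outcome would then be silent on the hypothesis that shaped recruitment. The question would rest on the proportion analysis, which compares groups within one mode at a time. rTMS responders were classified by having reported less pain after earlier stimulation. They may therefore differ from non-responders in placebo response or reporting under any mode, sham included. Each patient has a sham period that could remove such a difference, but the group comparison does not use it.

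**Working it through.** **1. The protocol's own figure.** Two-tailed Fisher's exact test on 8/12 against 2/12 gives p = 0.0361, which agrees with the stated 0.036.

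**2. What the model as listed can estimate.** Assume, for illustration only, that the true anodal-sham effect is -2 NRS units in responders and 0 in non-responders, and that cathodal equals sham in both.
- Common anodal-sham contrast, 12 per group: (12 × (-2) + 12 × 0)/24 = -1.
- Responder-group coefficient: (-2 + 0 + 0)/3 = -0.67, plus any underlying difference in pain level.
- True difference between groups in anodal-sham: -2 - 0 = -2. No coefficient or contrast in the model corresponds to it.

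A simulation of 400 balanced three-period, six-sequence crossovers (assumed within-patient SD 1, between-patient SD 1.5) gave a mean pooled contrast of -0.99. With the interaction added, the mean estimate of the group difference was -2.09.

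**3. What the proportion analysis can show.** Assume response probabilities of 8/12 in responders and 2/12 in non-responders under every mode, so that there is no tDCS-specific difference. Summing binomial probabilities over all 2 × 2 tables with 12 per group, the anodal Fisher test reaches p ≤ 0.05 with probability 0.614. A significant anodal result is therefore no evidence that the effect over sham differs by group.

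**4. Precision of the missing estimate.** Inputs: 12 per group (Study design), three periods, complete data, order balanced within group, and residual SD σ. The documents give no SD, so σ is assumed to be 1.0 to 2.0.
- Pooled anodal-sham: SE = σ√(2/24) = 0.289σ.
- Within one group: SE = σ√(2/12) = 0.408σ.
- Difference between groups: SE = σ√(2/12 + 2/12) = 0.577σ.
- Residual df = 72 observations - 24 patients - 2 (mode) - 2 (period) - 2 (interaction) = 42, so the two-sided 5% critical t is 2.018.

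| Assumed σ | SE of group difference | 95% CI half-width (2.018 × SE) | Power for a 2-unit difference |
|---|---|---|---|
| 1.0 | 0.577 | 1.2 | 92% |
| 1.5 | 0.866 | 1.7 | 62% |
| 2.0 | 1.155 | 2.3 | 39% |

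Power is from the non-central t with 42 df, two-sided 5%. These values are optimistic if data are missing or if the treatment effect varies between patients within a group.

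**The case against.** The strongest reply has four parts.

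- **The pooled contrast answers a stated question.** The abstract puts overall efficacy first, and the primary outcome is defined by mode without a split by group. This stands. A reader might infer that the model addresses something the trial never asked, and the documents do not support that.
- **The pooled estimate is not said to apply to each group.** A reader might infer that the plan would report -1 as the effect in both groups, and so credit non-responders with a benefit they do not have. The text promises only pairwise comparisons over all patients. An average labelled as an average is not biased.
- **The hypothesis is worded as response, and the protocol has a response analysis.** It would be wrong to say that the groups are never compared. Because that analysis is run for sham too, an equal group difference under sham would be visible. It would not be formally tested, however, and dichotomising discards information in a sample of 24.
- **This is a pilot with no power calculation, reported in a condensed article.** The pilot status limits how much weight the interaction can carry, but a small study meant to inform later ones still needs the estimate and its CI. Condensation is a weak defence, because the article lists the model terms down to sequence and nesting, and responder group is named as a main effect.

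**Conclusion.** The point holds in a limited form. The mixed model as listed estimates a pooled mode effect, which is a legitimate target. It cannot estimate or test whether the tDCS effect differs between rTMS responders and non-responders, which is the hypothesis under Aims. The proportion analysis does not close the gap, because it cannot separate a tDCS-specific difference from a general group difference in placebo response or reporting.

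That the term is absent, and what its absence implies, follows from the listed terms and needs no assumed figures. The sizes do rest on assumptions: effects of -2 and 0 for the illustration, equal response rates in all modes for the 61%, and σ of 1.0 to 2.0 with complete balanced data for precision and power. A reader might also infer that the interaction should replace the pooled contrasts as the main result. With a standard error twice as large and no power basis in the protocol, the documents do not support that.

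**What to change.** Add mode × responder group to the fixed effects. From that model report anodal-sham, cathodal-sham and anodal-cathodal within each rTMS group with 95% CIs. Report the between-group difference in anodal-sham, with its CI, as the estimate that addresses the hypothesis under Aims. Keep the pooled contrasts for overall efficacy and the proportion analysis as planned, and present all three together. Label the interaction exploratory.

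The change costs 2 df and some wording, with no new data, patients or visits. The price is precision. Group-specific intervals are about 1.4 times as wide as the pooled one (0.408/0.289), and the interval for the difference between groups is twice as wide (0.577/0.289). An interval that includes zero should therefore not be read as showing that the two groups respond alike.

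### The three-week window for the pre-post pain change does not match the primary outcome and cannot be filled in period 3 from the scheduled diaries

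*Protocol article*

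**What the plan says.** Several sections of the protocol article bear on when pain is measured.

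- **Primary and secondary outcome measures:** "The primary outcome measure will be the mean daily pain intensity during each mode of tDCS". No number of days is given. The period of use could mean the 5 consecutive stimulation days or the 2 weeks for which the patient holds the device.
- **Initial and follow-up assessments:** "Pain diaries will be filled out daily for 1 week at baseline and for 14 days beginning at each stimulation period".
- **Abstract, Methods/design:** "A linear mixed model with fixed effects will analyse changes in pain scores from pre- to post- interventions".
- **Statistical analysis:** here "the model will be first fitted with the pain intensity data", and the change score, where required, compares run-in pain with "pain over 3 consecutive weeks following tDCS treatment". The responder rule in the same section is a reduction from run-in baseline of at least 2 units or 30%. It states no window.
- **Study flow:** a daily diary is kept through each of the two 4-week wash-outs, which follow periods 1 and 2. After the third device return (visit 6) no diary is mentioned. "The final visit (7) will happen in a further 2" weeks. Later one-week diaries belong to patients who choose to go on using the device daily.

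**The concern.** The outcome section measures pain during a mode; the change score measures it afterwards, over a longer span. The abstract presents the change as what the mixed model analyses, and the responder analysis is built on a change too. The three-week window therefore competes with the primary definition and is not merely side text.

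The second difficulty is practical. A 21-day post-treatment window needs diary days that the stated schedule supplies after periods 1 and 2 but not after period 3. If the rule is applied as written, each patient's third mode is averaged over different days from the other two. The same diaries could also give different effects and responder counts according to which window is picked, and that choice should not be open once data are seen.

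**Working it through.** **The plan's own figure.** The only computed figure in the article is the illustrative Fisher test, 8/12 against 2/12, two-tailed p = 0.036. With 10 responders among 24, the tail is [C(12,8)·C(12,2) + C(12,9)·C(12,1) + C(12,10)·C(12,0)] / C(24,10) = (32,670 + 2,640 + 66) / 1,961,256 = 0.01804. Doubling gives 0.0361, so the figure reproduces. The window problem does not depend on it.

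**Does level or change matter in itself?** Let B be a patient's run-in mean and Y(p) the mean in period p. The change is D(p) = B − Y(p), so D(p) − D(q) = Y(q) − Y(p). There is one run-in baseline, so it cancels from within-patient contrasts when data are complete. The conflict that matters is therefore the days over which Y is averaged.

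**Inputs for the diary count.** Day 1 is the first stimulation of a period.

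- Stimulation: days 1-5 (Determination of the stimulation site).
- Diary in every period: days 1-14 (Initial and follow-up assessments).
- Wash-out diary after periods 1 and 2: 4 weeks, days 15-42 (Study flow).
- Period 3 after device return: no diary stated; visit 7 at about day 14 + 14 = 28 (Study flow).

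**Count.** Days available = number of days from the window start s to s + 20 that lie on or before the last diary day (42 for periods 1 and 2; 14 for period 3 as scheduled; 28 if a diary ran to visit 7, which is an assumption).

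| Window starts | Days needed | Periods 1 and 2 | Period 3, as scheduled | Period 3, if diary ran to visit 7 |
|---|---|---|---|---|
| Day 1 | 1-21 | 21 of 21 | 14 of 21 | 21 of 21 |
| Day 6 (after fifth session) | 6-26 | 21 of 21 | 14 − 5 = 9 of 21 | 21 of 21 |
| Day 15 (after device return) | 15-35 | 21 of 21 | 0 of 21 | 28 − 14 = 14 of 21 |

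No choice of start day fills the window in period 3 from the scheduled diaries. By contrast, days 1-14 give 14 of 14 in all three periods.

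**Consequence for the analyses.** The mixed model has a fixed effect for period, which removes a shift common to all modes in period 3. It does not correct for a mode difference that is larger or smaller over days 6-14 than over days 6-26; that is a mode-by-period difference, and the model has no term for it. The proportion analysis is done separately for each mode, and no period adjustment is stated.

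**Sensitivity of small counts.** In the plan's own example, moving one patient (7/12 against 2/12) gives a tail of [C(12,7)·C(12,2) + C(12,8)·C(12,1) + C(12,9)·C(12,0)] / C(24,9) = (52,272 + 5,940 + 220) / 1,307,504 = 0.0447, so p = 0.089. This illustrates sensitivity to classification. It is not a forecast of how many patients would be reclassified.

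**The case against.** The best defence is that the primary outcome is usable as it stands. The outcome definition, the 14-day diary and the 2 weeks of device possession together point to a window collected identically in all periods, and the statistical section fits the model to pain intensity first. The three weeks attach only to a change score computed where required. This largely stands: a reader might infer that the primary outcome itself cannot be measured in period 3, and the documents do not support that. What remains is that the abstract names change as what the model analyses, and that the responder rule is a change with no other window.

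A condensed article may also have left out a diary between visits 6 and 7. With 5 stimulation days, counting from day 6 is the natural reading, and a diary to visit 7 would fill it. The shortfall is thus in the stated diaries and not necessarily in calendar follow-up. Even so, such a diary would leave a window starting at device return one week short.

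Three stronger readings should be resisted.

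- A reader might infer that wash-out days are counted as treatment days. The text says the window follows treatment, so they are not.
- A reader might infer that the modes are observed for unequal times. The shortfall follows period, not mode; the order is randomised, and period and sequence are in the model.
- A reader might try to state what share of the effect each window captures. That needs a duration of effect. The Background gives about 2 weeks for rTMS but several weeks for tDCS, so no single figure is supported.

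Finally, the weekly mean in the sample-size illustration ("weekly mean reduction of 30% or 2 units on NRS") may be only an averaging unit and is weak evidence of yet another window.

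**Conclusion.** The point holds in a limited form. The article gives incompatible windows for pain and does not say which one feeds the pre-post change named in the abstract or the responder rule. The three-week window is complete in periods 1 and 2 (21 of 21 days) but not in period 3 (9, 0 or at most 14 of 21, depending on the start day). Applied as written, it averages period 3 over different days, which adds noise and can distort mode contrasts. The size of that distortion cannot be derived from the documents, and no systematic bias for or against any mode is shown.

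The counts assume that the diary starts on the first stimulation day, that the device is returned at about day 14, and that no unstated diary is kept after visit 6. This should be fixed. It does not undermine a self-described pilot whose days 1-14 data are collected alike in every period.

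**What to change.** Name one window, the mean daily NRS over days 1-14 from the first stimulation of each period, and use it for the primary model, the change score (against the run-in mean) and the responder rule. Align the abstract, the outcome section and the statistical section with it. The diary schedule already collects these days identically in all three periods, so it also serves patients who have already finished.

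If a three-week post-treatment window is still wanted, make it secondary, start it on day 6 in every period, and state that the daily diary continues from visit 6 to visit 7. Patients who completed period 3 without that diary would lack those days.

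The main change costs only wording and should be made before unblinding. The optional one costs 2 more weeks of an existing diary in period 3.
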